## Abstract

**Background::**

Anticoagulant therapy is used for stroke prevention and proved to be effective and safe in the long term. The study aims to analyse the cost-effectiveness relationship of using of direct-acting oral anticoagulants vs vitamin K antagonists to prevent ischaemic stroke in patients with nonvalvular atrial fibrillation, including all the active ingredients marketed in Spain, prescribed for 2 years in the Primary Care service of the *Institut Català de la Salut*.

**Methods::**

Population-based cohort study, in which the cost of the 2 treatment groups will be evaluated. Direct costs (pharmacy, primary care, emergency and hospitalization) and indirect costs (lost productivity) will be included from a social perspective. Effectiveness (assessed as the occurrence of a health event, the 1 of primary interest being stroke) will be determined, with a 2-year time horizon and a 3% discount rate. The average cost of the 2 groups of drugs will be compared using a regression model to determine the factors with the greatest influence on determining costs. We will carry out a univariate (‘one-way’) deterministic sensitivity analysis.

**Discussion::**

We hope to provide relevant information about direct and indirect costs of oral anticoagulants, which, together with aspects of effectiveness and safety, could help shape the consensual decision-making of evaluating bodies.

## Introduction

1

Atrial fibrillation (AF) is the most common arrhythmia in western countries and is associated with high morbidity and mortality, thereby constituting a major public health problem.^[1,2]^ It is 1 of the most frequent causes of ischaemic stroke.^[3,4]^ Anticoagulant therapy is used for stroke prevention, for which there are 2 main groups of drugs —vitamin K antagonists (VKAs) and direct-acting oral anticoagulants (DOACs)— which have both proved effective and safe in the long term.^[5]^

VKAs have been widely used for a long time and their efficacy in preventing strokes and systemic embolism in patients with nonvalvular atrial fibrillation (NVAF) is well established.^[6]^ However, most of the studies have involved warfarin, and the results have been generalized to all VKAs.^[7]^ The price of these drugs is low (compared with that of DOACs),^[8]^ although they generate direct and indirect costs. Furthermore, they have limitations such as interindividual and intraindividual variability of response, a slow onset of action, a narrow therapeutic margin, a need for dose-adjustment through periodic controls of the international normalized ratio, and interactions with some foods and medications.^[9–11]^

In recent years, DOACs have emerged that have more predictable anticoagulant effects and fewer interactions with other drugs, and that allow a fixed dosage regimen, without the need for monitoring.^[12]^ Overall, DOACs present a favorable risk prevention profile, with significantly lower levels of strokes, intracranial haemorrhages and mortality compared with VKAs, but they have a higher risk of gastrointestinal bleeding^[7]^ and are expensive.^[8]^ It is also important to take into account the adjustment of the dosage according to age, weight, and renal function, in addition to monitoring compliance, because highly variable therapeutic adherence rates have been noted.^[7,13]^

The European and American guidelines recommend the use of any DOACs rather than VKAs because of their net clinical benefit, except in selected cases.^[14–16]^ However, the use of DOACs in clinical practice is determined by the recommendations of the health authorities of each country. In Spain, VKAs are recommended as the first choice, with DOACs being used when specifically recommended,^[17]^ although currently it has been observed that more than 80% of physicians are starting treatments with DOACs .^[18]^

Previous studies found that DOACs tend to be more cost-effective than VKAs for the treatment of AF.^[19–23]^ One of these studies suggest that rivaroxaban is cost-effective compared to VKA, although the type of AVK and the dose thereof are not specified.^[23]^ A comparative study of the cost-utility of the first 3 DOACs to be marketed in Spain (apixaban, dabigatran and rivaroxaban),^[24]^ found dabigatran to be the most cost-useful. ^[25]^ However, the most recent study carried out in Spain does not show significant differences between dabigatran and AVKs.^[26]^ A recent study of edoxaban in Spain concluded that it is a cost-effective alternative for this indication.^[27]^ However, we did not find any cost-effectiveness studies that included all the anticoagulants currently available on the market, with a population base (without economic models) and real world data (RWD).

The main objective of the study will be to analyse the cost-effectiveness of using DOACs in comparison with VKAs to prevent ischaemic stroke in patients with NVAF, including all the active ingredients marketed in Spain prescribed for 2 years in the Primary Care (PC) service of the *Institut Català de la Salut* (ICS). As secondary objectives, we intend to:

(1)determine the appearance of a health event, according to the type of anticoagulation used (VKA or DOAC), and the factors related to this;(2)evaluate the cost in patients who are poorly controlled by VKAs and under-treated with DOACs; and(3)analyse the factors associated with increased costs.

The present study protocol, named FantasTIC (Non-valvular atrial fibrillation and treatment, health assessment, Information and Communication Technologies) study has been designed to address these aspects.

## Methodology

2

### Design and study period

2.1

This is a population-based cohort study designed to evaluate and compare the cost-effectiveness of the 2 types of anticoagulant treatment (VKA and DOAC) in patients with NVAF, with a time horizon of 2 years (from 1 January 2017 until 31 December 2018). The flow diagram of the study is presented in Figure 1.

**Figure 1 F1:**
[figure not shown]
Flow diagram.

### Study population

2.2

Our study population will be that treated by the PC service of the ICS. The Autonomous Community of Catalonia has a health service whose main provider is the ICS, in which PC is organized into teams made up of family doctors, nurses, paediatricians, social workers, dentists and support staff. The ICS manages, among others, 287 PC centres (PCCs) to which 5,564,292 citizens are assigned (approximately 80% of the Catalan population).^[28]^

As established by the *Sistema de Información para el Desarrollo de la Investigación en Atención Primaria* (SIDIAP; Information System for the Development of Research in PC), during the year 2017, 126,702 cases of NVAF had been registered in the ICS, 61,002 of which were receiving anticoagulant treatment (41,430 VKA and 19,548 DOAC).

Inclusion criteria:

(1)Patient with a diagnosis of NVAF at least 1 year old.(2)Patient undergoing treatment with VKA or DOAC.

Exclusion criteria:

(1)Patient with indications for anticoagulation other than NVAF.(2)Pregnancy.

Data collection will end on 31 December 2018 or sooner if any of the following occurs:

(1)Anticoagulation prescription suspended for more than 180 days.(2)Patient moves to another Autonomous Community.(3)Patient becomes pregnant.(4)Withdrawal of the diagnosis of NVAF.(5)Appearance of a diagnosis of valvular AF.(6)Death of the patient.

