### Cost estimation

2.5

Cost estimates will take into account direct expenses (from pharmacy, PC, emergencies and hospitalisation) and indirect expenses (loss of productivity), from a social perspective, in patients diagnosed with NVAF and treatment with oral anticoagulants. Two groups will be established: patients receiving VKAs and those receiving DOACs. We will use a 3% discount rate, which will be applied in the second year.

We will use the charges set out in the *Diari Oficial de la Generalitat de Catalunya* (DOGC)^[32]^ closest to the date of analysis (2014) to estimate the costs. The euro will be used as the reference currency (which will not require conversion). Prices will be adjusted to those of 2018 to take into account inflation in the health sector.^[33]^ The costs of hospital admissions will be obtained from the *Grups Relacionats amb el Diagnòstic* (GRD) patient classification system, published in the DOGC.^[34,35]^ For drug prices, the retail price taken from pharmacy billing data will be used. The final costs of the 2 study groups (patients treated with VKAs and those treated with DOACs) will be calculated by quantifying the resources consumed by each individual with respect to each variable and then multiplying by the cost of each resource. This procedure will yield the total cost of the resource per individual, as well as the total cost for each study group.

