### Measurement of effectiveness

2.6

The primary health event in this project will be “ischaemic stroke” and the indicator of cost-effectiveness will be “avoided strokes”. To estimate avoided strokes we will determine the total economic cost for the 2 pharmacological groups, as well as the number of strokes registered during the 2 years of the study period. Finally, we will compare the groups and thereby determine the economic cost of avoiding a stroke.

Secondarily, we will determine the appearance of the following health events during the 2 years of the study:

Ischaemic events:(1)Ischemic stroke.(2)Other thromboembolic events (transient ischaemic attack (TIA), angina, acute myocardial infarction, and peripheral embolism).•Haemorrhagic events:(1)Intracranial haemorrhage.(2)Gastrointestinal bleeding.(3)Other haemorrhages.•All-cause mortality.

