### Economic analysis

2.7

The cost of DOACs will be compared with that of VKAs, following the methodological guidelines for this type of study proposed by the International Society for Pharmacoeconomics and Outcomes Research (ISPOR)^[36]^ and the International Network of Agencies for Health Technology Assessment (INAHTA).^[37]^

After comparing the average cost of both groups of drugs and estimating their confidence intervals, a regression model will be developed to determine which factors may have the most substantial influence on determining costs. A generalized linear model (GLM) will be derived, which, given the asymmetry of the cost variable, will be based on the gamma family of distributions, with a log link function,^[38]^ because these give a best fit to the data when estimating the impact of the factors associated with the composition of patient costs.

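### Accumulated costs and stroke counts are compared over a 2-year horizon without using time observed, although five reasons other than death can end follow-up early

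*Protocol article*

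**What the plan says.** All references are to the protocol article.

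- Section 2.1 sets the design "with a time horizon of 2 years (from 1 January 2017 until 31 December 2018".
- Section 2.2 states: "Data collection will end on 31 December 2018 or sooner if any of the following occurs". Six reasons follow. One is death. The other five are "Anticoagulation prescription suspended for more than 180 days", a move to another region, pregnancy, withdrawal of the NVAF diagnosis, and a new diagnosis of valvular AF.
- Section 2.5 multiplies each person's resource use by unit cost and adds up: "This procedure will yield the total cost of the resource per individual, as well as the total cost for each study group".
- Section 2.6 takes as its effect measure "the number of strokes registered during the 2 years of the study period" and derives the cost of avoiding a stroke by comparing the groups.
- Section 2.7 begins "After comparing the average cost of both groups of drugs and estimating their confidence intervals" and then turns to the factors that drive cost: "A generalized linear model (GLM) will be derived, which, given the asymmetry of the cost variable, will be based on the gamma family". The link is logarithmic. No offset or weight for time observed is named.
- Section 2.8 limits the sensitivity analysis to cost items and prices. Section 4.1 does not list incomplete follow-up among the limitations.
- Section 2.4 names follow-up as one of five groups of variables. Its Table 1 is not shown, and none of sections 2.5 to 2.8 uses a follow-up time.

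**The concern.** A patient who moves away or is taken off anticoagulation partway through contributes only part of a 2-year cost and has had only part of the 2 years in which a stroke could be registered. If the accumulated total and the stroke count enter the comparison as they stand, that patient counts as a cheaper patient without a stroke. Two consequences follow.

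1. The absolute 2-year cost and stroke risk of each group are too low.
2. If such early ends are more frequent on one drug, or fall on patients with a different prognosis, the contrast between groups shifts too. The group that stops sooner looks cheaper and better protected.

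The second consequence is plausible here. Suspension of treatment is itself an end-of-follow-up rule, and the Introduction says of DOACs that "highly variable therapeutic adherence rates have been noted". At stake is the study's headline quantity, the cost per stroke avoided, whose numerator and denominator are both affected.

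**Working it through.** **Design figures.** The article gives no early-end rate, stroke rate, mean cost or expected difference, so there is no figure to reproduce. From the article come only the horizon (24 months), the end-of-follow-up rules, and the way costs and strokes are summed. Every rate and cost below is an assumption.

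**Check 1: simple proportion.** Assume a true cost of EUR 4,000 per 24 months in both groups, accruing evenly, with mean observed follow-up of 22 and 20 months and no deaths.

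- 4,000 × 22/24 = 3,667
- 4,000 × 20/24 = 3,333
- spurious difference = 333
- each month of difference in follow-up: 4,000/24 = 167

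**Check 2: constant hazards over 2 years.** Let c be the proportion whose follow-up ends early for reasons other than death, and r the yearly stroke rate.

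- early-end hazard L = −ln(1 − c)/2
- person-years per patient = (1 − exp(−2L))/L
- observed stroke risk = r/(r + L) × (1 − exp(−2(r + L)))
- observed cost = yearly cost × person-years

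Assumed: r = 1.5 per 100 person-years on VKA; on DOAC either 1.5 (no effect) or 1.2 (rate ratio 0.80); yearly cost EUR 1,500 on VKA and 2,000 on DOAC.

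Example with c = 10% on VKA and 20% on DOAC, no true effect:

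- person-years 1.898 and 1.793
- costs 1,500 × 1.898 = 2,847 and 2,000 × 1.793 = 3,585 (from unrounded person-years), difference 738; with complete follow-up it is 4,000 − 3,000 = 1,000
- risks 2.806% and 2.650%, apparent risk ratio 0.945, that is 1.55 strokes per 1,000 apparently avoided when none are

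| True rate ratio | Early end, VKA / DOAC | Apparent risk ratio | Strokes avoided per 1,000 | Cost difference (EUR) | Cost per stroke avoided (EUR) |
|---|---|---|---|---|---|
| 1.00 | 0% / 0% | 1.000 | 0 | 1,000 | undefined |
| 1.00 | 10% / 20% | 0.945 | 1.55 | 738 | about 475,000 |
| 1.00 | 10% / 30% | 0.887 | 3.18 | 517 | about 163,000 |
| 1.00 | 30% / 10% | 1.128 | −3.18 | 1,273 | negative |
| 0.80 | 0% / 0% | 0.802 | 5.84 | 1,000 | about 171,000 |
| 0.80 | 20% / 20% | 0.802 | 5.24 | 896 | about 171,000 |
| 0.80 | 10% / 30% | 0.711 | 8.10 | 517 | about 64,000 |
| 0.80 | 30% / 10% | 0.905 | 2.37 | 1,273 | about 538,000 |

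**Reading.** With 20% early end in both groups, absolute costs are understated by 1 − 1.793/2 = 10.4%, but the risk ratio and the cost per stroke avoided barely move. With unequal early end, the cost per stroke avoided moves from about 171,000 to between 64,000 and 538,000. Dividing strokes by person-years brings the ratio back to 0.80 (or 1.00 when there is no effect) in every row, so the distortion comes from ignoring time observed.

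**The case against.** **The article is condensed.** It nowhere says that every patient is treated as having contributed 2 years. Section 2.6 fixes no denominator for strokes, and with 41,430 VKA and 19,548 DOAC patients one must follow somewhere. Follow-up variables are planned. A full protocol or analysis plan may settle the matter. This has weight, but sections 2.5 to 2.7 do more than stay silent: they set out the main calculation step by step, and carrying it out as written gives truncated totals labelled as 2-year results.

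**Death.** A reader might infer that all six reasons bias the comparison, and that the group dying sooner looks falsely cheap. The article does not support that. A patient who dies has no later cost and can have no later stroke, so cost accumulated to death is the complete 2-year cost, and the proportion with a stroke already treats death as a competing event. This part of the objection stands in full, and the concern is confined to the other five reasons.

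**The group contrast is not necessarily biased.** A reader might also infer that the comparison must be wrong. With equal early end unrelated to prognosis, the cost per stroke avoided is practically unchanged, as the 20% / 20% row shows. This stands too.

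**The illustrations are demanding.** Under a constant hazard, mean follow-up of 22 and 20 months needs about 16% and 31% early end, none of it death. Suspension must also exceed 180 days before it counts, and the article does not say whether the end date is then set back to the start of the suspension. The true effect could be smaller than shown.

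**Conclusion.** The point holds in a limited form. The early-end rules of section 2.2 and the calculation in sections 2.5 to 2.7 do not fit together. Wherever follow-up ends early for one of the five reasons other than death, absolute 2-year costs and stroke risks are understated. The cost difference and the cost per stroke avoided are biased only if those early ends differ by drug group or are related to prognosis. That is plausible because suspension of the study drugs is one of the reasons, but the article neither shows nor excludes it. Size and direction cannot be determined from the document. The spurious EUR 333, and the range of about EUR 64,000 to 538,000 around 171,000 per stroke avoided, show only what unequal follow-up could do under the stated assumptions. They are not estimates for this cohort. Since the main result is exposed and the remedy is cheap, the plan should be corrected before analysis.

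**What to change.** Amend sections 2.5 to 2.7 as follows.

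1. Define the outcomes as mean cost over 2 years and the 2-year cumulative incidence of first ischaemic stroke, with death as a competing event.
2. Estimate both with a method that adjusts for censoring. One suitable choice is inverse-probability-of-censoring weighting with costs partitioned by interval. Count deaths as complete observations and only the other five reasons as censoring. Other censoring-adjusted estimators would also serve.
3. Use the same weights in the gamma model.
4. Tabulate person-time and reason for end of follow-up by drug group, so that readers can see whether follow-up was unequal.

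The cost is revised wording, some extra programming and slightly wider confidence intervals. No new data source appears necessary: section 2.3 already provides for prescriptions, dispensing and dates of death. The weighting relies on recorded patient characteristics explaining why follow-up ended, and this assumption should be stated.

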### Data source

2.3

At ICS, more than 9175 professionals working in PC use the same computerized medical history program, called eCAP. eCAP data will be obtained through SIDIAP, which is a unique database, previously validated, and highly representative of the Catalan population.^[29,30]^

In this way, SIDIAP provides, from each of the 5.8 million citizens assigned to the various PCCs of the ICS, information linked to a unique, anonymised identifier. The following information will be obtained from all NVAF patients receiving anticoagulants on January 1, 2017:

(1)data from the eCAP program: demographic data, PC visits, health events, clinical variables, referrals, deaths, prescriptions and sick leave;(2)laboratory results: these will be extracted directly from the laboratory database, rather than depending on manual records, thereby guaranteeing data quality;(3)medication dispensed by pharmacy offices: this information will be obtained directly from those offices;(4)other, external sources of information: (4.1.) *Conjunt Minim Bàsic de Dades* (CMBD), which is a population registry that collects ICD-9 pathology data linked to hospitalization at all of the Hospitals in Catalonia,^[31]^ (4.2.) Mortality: data supplied by the Department of Health, including cause and date of all deaths of residents of Catalonia.^[28]^

### Variables

2.4

The variables considered in the study will be divided into 5 groups: cost, follow-up, effectiveness, pharmacy, and those corresponding to personal history (summarised in Table 1).

**Table 1 T1:**
[figure not shown]
Variables, sampling period, and source of information.

All oral anticoagulants that are marketed in Spain will be included in the study:

(1)VKAs: Acenocoumarol and warfarin.(2)DOACs: Apixaban, dabigatran, edoxaban and rivaroxaban.

### Cost estimation

2.5

Cost estimates will take into account direct expenses (from pharmacy, PC, emergencies and hospitalisation) and indirect expenses (loss of productivity), from a social perspective, in patients diagnosed with NVAF and treatment with oral anticoagulants. Two groups will be established: patients receiving VKAs and those receiving DOACs. We will use a 3% discount rate, which will be applied in the second year.

We will use the charges set out in the *Diari Oficial de la Generalitat de Catalunya* (DOGC)^[32]^ closest to the date of analysis (2014) to estimate the costs. The euro will be used as the reference currency (which will not require conversion). Prices will be adjusted to those of 2018 to take into account inflation in the health sector.^[33]^ The costs of hospital admissions will be obtained from the *Grups Relacionats amb el Diagnòstic* (GRD) patient classification system, published in the DOGC.^[34,35]^ For drug prices, the retail price taken from pharmacy billing data will be used. The final costs of the 2 study groups (patients treated with VKAs and those treated with DOACs) will be calculated by quantifying the resources consumed by each individual with respect to each variable and then multiplying by the cost of each resource. This procedure will yield the total cost of the resource per individual, as well as the total cost for each study group.

### Measurement of effectiveness

2.6

The primary health event in this project will be “ischaemic stroke” and the indicator of cost-effectiveness will be “avoided strokes”. To estimate avoided strokes we will determine the total economic cost for the 2 pharmacological groups, as well as the number of strokes registered during the 2 years of the study period. Finally, we will compare the groups and thereby determine the economic cost of avoiding a stroke.

Secondarily, we will determine the appearance of the following health events during the 2 years of the study:

Ischaemic events:(1)Ischemic stroke.(2)Other thromboembolic events (transient ischaemic attack (TIA), angina, acute myocardial infarction, and peripheral embolism).•Haemorrhagic events:(1)Intracranial haemorrhage.(2)Gastrointestinal bleeding.(3)Other haemorrhages.•All-cause mortality.

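### The cost per stroke avoided is defined as a plain comparison of non-randomised VKA and DOAC groups, with no confounder adjustment tied to it; confounding could bias the ratio materially and might reverse its sign.

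*Protocol article*

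**What the plan says.** The Design and study period section describes an observational comparison: "This is a population-based cohort study designed to evaluate and compare the cost-effectiveness of the 2 types of anticoagulant treatment". Under Data source, the cohort consists of "all NVAF patients receiving anticoagulants on January 1, 2017", that is, prevalent users rather than new starters.

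The main result is defined in Measurement of effectiveness. For each drug group the investigators take the total cost, "as well as the number of strokes registered during the 2 years of the study period", and then: "Finally, we will compare the groups and thereby determine the economic cost of avoiding a stroke". On the cost side, Economic analysis gives the order of work: "After comparing the average cost of both groups of drugs and estimating their confidence intervals, a regression model will be developed". That model is a generalised linear model (gamma family, log link) for cost. Its stated purpose is to find what drives cost.

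On how patients come to be in each group, the Introduction says: "In Spain, VKAs are recommended as the first choice, with DOACs being used when specifically recommended". The same sentence adds that "it has been observed that more than 80% of physicians are starting treatments with DOACs".

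**The concern.** In a non-randomised cohort, a difference in strokes or in cost between VKA and DOAC users mixes the effect of the drug with differences in who receives it. The article ties no matching, weighting, propensity score or adjusted stroke model to the cost per stroke avoided.

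Baseline differences are likely on either reading of the Introduction. If prescribers follow the recommendation, DOAC users are those with a specific reason to receive one. If most prescribers now start with a DOAC, a cohort of existing users on 1 January 2017 may set long-standing VKA patients against more recent DOAC starters.

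Nothing later in the plan would reveal the problem. The Sensitivity analysis section varies cost items and uncertain prices only. The Limitations section covers under-registration, uncounted costs and the short horizon, but not confounding.

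The ratio is sensitive because its denominator is a small difference between two small risks. A modest bias in the stroke comparison can change the cost per stroke avoided severalfold, or change its sign. The authors expect the result to inform evaluating bodies.

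**Working it through.** **The plan's own figures.** The article gives no stroke rate, effect size, cost difference or power calculation, so there is no design figure to reproduce. The only relevant counts are "61,002 of which were receiving anticoagulant treatment (41,430 VKA and 19,548 DOAC". The two groups add to 41,430 + 19,548 = 60,978, which is 24 (0.04%) below 61,002 and immaterial here.

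**Illustration 1: one binary confounder (all inputs assumed).** Let prior stroke be present in a share pV of VKA users and pD of DOAC users, and let it multiply stroke risk by m.

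Bias factor B = [1 + pD(m − 1)] / [1 + pV(m − 1)]; crude RR = true RR × B. Take pV = 0.10 and a true RR of 0.90.

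| pD | m | B | Crude RR |
|---|---|---|---|
| 0.15 | 2.0 | 1.15/1.10 = 1.045 | 0.94 |
| 0.15 | 2.5 | 1.225/1.15 = 1.065 | 0.96 |
| 0.15 | 3.0 | 1.30/1.20 = 1.083 | 0.975 |
| 0.20 | 2.0 | 1.20/1.10 = 1.091 | 0.98 |
| 0.20 | 2.5 | 1.30/1.15 = 1.130 | 1.02 |
| 0.20 | 3.0 | 1.40/1.20 = 1.167 | 1.05 |

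Reversal requires B > 1/0.90 = 1.11. With pD = 0.20 this needs m > 2.25. With pD = 0.15 it needs m of about 3.9, outside the range. Two of the six cells reverse. A true RR of 0.80 would need B > 1.25, which no cell reaches.

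The mildest cell still matters. With an assumed 2-year VKA risk of 2.5%, the true effect is 25 × 0.10 = 2.5 strokes avoided per 1,000. At a crude RR of 0.941 it appears as 25 × 0.059 ≈ 1.5. At a fixed incremental cost, the cost per stroke avoided rises by 2.5/1.5, about 1.7-fold.

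**The other direction.** Swap the shares (prior stroke in 15–20% of VKA and 10% of DOAC users). B becomes the reciprocal, 1/1.167 to 1/1.045 = 0.857 to 0.957, and a true RR of 0.90 appears as 0.77–0.86. DOACs would then look better than they are.

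**Illustration 2: two risk strata (all inputs assumed).** VKA 2-year stroke risk is 1% (low) or 3% (high), the true RR is 0.80, and 40% of VKA users are high-risk.
- Crude VKA risk = 0.6 × 1% + 0.4 × 3% = 1.80%.
- With 60% of DOAC users high-risk: 0.8 × (0.4 × 1% + 0.6 × 3%) = 1.76%, so 0.4 strokes avoided per 1,000.
- Standardised to the pooled groups: high-risk share (0.4 × 41,430 + 0.6 × 19,548)/60,978 = 0.464; VKA risk 1% + 2% × 0.464 = 1.93%; strokes avoided 0.2 × 19.3 ≈ 3.9 per 1,000.
- At an assumed extra cost of EUR 800 per patient: 800/0.0004 = EUR 2.0 million crude, against 800/0.00386 ≈ EUR 0.21 million standardised.
- The sign flips once the DOAC high-risk share exceeds 62.5%, or 50% if the true RR is 0.90. If the high stratum has only twice the low risk, these thresholds are 75% and 55.6%.

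**Counts and denominators.** At an identical assumed risk of 3%, the groups would register about 41,430 × 0.03 = 1,243 and 19,548 × 0.03 = 586 strokes. The effect must therefore be stated as a risk per patient.

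**The case against.** The strongest defence is that this is a condensed article. Covariate lists, propensity models and balance checks normally sit in an analysis plan that is not shown, and their absence here is no fault. That stands for the details. It does not cover the definition of the primary quantity, which the article does give, as a group comparison, while assigning its one named regression to a different task.

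Second, a secondary objective covers health events by type of anticoagulant and the factors related to them, so some multivariable analysis of stroke may be intended. The article attaches no model to that objective and does not feed it into the ratio. The cited ISPOR and INAHTA guidelines likewise do not alter the stated computation.

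Third, the cost model's covariates are not listed. It could include treatment group and so yield an adjusted cost contrast. That is fair, but the article does not say the ratio will use it, and it would leave the stroke side untouched.

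Four stronger readings are tempting and are not supported:
- That the protocol prescribes an unadjusted analysis in so many words. It never uses that term; the reading rests on the computation it describes.
- That it reports the two groups to be at different stroke risk. The Introduction describes health-authority recommendations and a departure from them in practice; it gives no baseline risk by group.
- That stroke counts will be compared without denominators. The wording allows this, but costs are also computed per individual, so it cannot be assumed.
- That the personal-history variables go unused. The Variables section plans to collect them, and the table listing them is not shown.

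**Conclusion.** The point holds. Followed as written, the plan yields a cost per stroke avoided that carries whatever baseline differences exist between VKA and DOAC users, and no other part of the plan would detect or bound them. The main objective depends on this ratio, so the definition should be changed before the analysis is run.

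The size is not known from the documents. Under the assumed inputs of the first illustration, the bias factor is 1.045–1.167 and a true RR of 0.90 appears as 0.94–1.05; the swapped case biases it the other way. A reader might infer that the main result will be reversed, or that DOACs will appear dominated. The documents do not support that. Reversal occurs only in the upper part of an assumed range, the direction of confounding is not established, and dominance would also require DOACs to cost more overall, which is what the study sets out to measure.

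**What to change.** In sections 2.6 and 2.7, define the primary ratio as confounder-adjusted incremental cost divided by confounder-adjusted incremental 2-year stroke risk. State both per patient and estimate both in the same population. Use covariates dated before 1 January 2017, and name the method: propensity-score weighting, propensity-score matching and regression standardisation are all acceptable. If standardisation is chosen, the planned gamma model can supply the cost side and a stroke model must be added.

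Keep variables that arise after baseline, such as INR control or events during follow-up, out of the adjustment set. Report the crude ratio as descriptive only. Add residual confounding to the Limitations section.

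The cost is protocol wording, additional analysis and possibly slightly wider intervals. Personal-history variables are already planned, so new data collection is probably small, but the covariate list should be checked against Table 1.

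Suggested wording: *The cost per stroke avoided will be the adjusted difference in mean cost per patient divided by the adjusted difference in 2-year ischaemic stroke risk, both standardised to the same population using covariates recorded before 1 January 2017. The unadjusted ratio will be shown for description only.*
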